Chinese herbal medicine (CHM) has been used in Chinese NSCLC patients treated with EGFR-TKIs for more than 10 years and has demonstrated its efficacy in delaying EGFR-TKI resistance and alleviating adverse effects in a number of clinical trials (Yang et al., 2018; Jiao et al., 2019; Tang et al., 2019). CHM contains several active compounds that interact with target proteins involved in EGFR-TKI resistance (Bing et al., 2018). Our previous multi-center, double-blind, placebo-controlled clinical trial (CATLA study) confirmed that the addition of CHM (Yiqi-Yangyin-Jiedu decoction, YYJD) to EGFR-TKI (gefitinib, erlotinib, or icotinib) significantly prolongs progression-free survival (PFS) and improves the quality of life (QoL) in NSCLC patients (Jiao et al., 2019). These trials mainly involve first-generation EGFR-TKIs. Osimertinib, as a third-generation EGFR-TKI, inhibits EGFR-sensitive mutations (Ex19del and L858R) like the first-generation EGFR-TKI. Given their similar mechanisms of action, it is reasonable to expect CHM to have clinical benefits for osimertinib as well.

The current study (CATLA-2) will determine whether the addition of CHM YYJD to third-generation EGFR-TKI osimertinib (O+YYJD) prolongs PFS compared with osimertinib plus placebo (O+placebo) in advanced NSCLC patients who have an activating EGFR mutation.

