#### Inclusion Criteria

(1) Pathologically confirmed NSCLC (Health Commission of PRC and National Health Commission of the People’s Republic of China, 2019).(2) Locally advanced or metastatic NSCLC that is not amenable to curative surgery or radiotherapy.(3) The tumor has one of 2 common EGFR mutations known to be associated with EGFR-TKI sensitivity (Ex19del, L858R).(4) Patients must have no treatment for locally advanced or metastatic NSCLC.(5) Aged 18–74 years old.(6) No major organ dysfunction: hemoglobin ≥120 g/L, absolute neutrophil count (ANC) ≥1.5 × 10^9^/L, platelets ≥80 × 10^9^/L, bilirubin ≤ 1.5ULN, alkaline phosphatase (AP), aspartate aminotransferase (AST), and alanine aminotransferase (ALT) ≤ 2.5 × ULN. INR ≤ 1.5, creatinine ≤ 1.5 × ULN.(7) Provision of informed consent forms.

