#### Exclusion Criteria

(1) Those with a history of other malignancies within 5 years;(2) Those with symptomatic brain metastases;(3) Those with congestive heart failure (> class II NYHA heart function), unstable (angina at rest), initial onset (starting within 3 months), angina pectoris, or myocardial infarction occurring within 6 months;(4) Those with active infection (> Grade 2 adverse events according to CTCAE.5.0 version);(5) Those with a history of uncontrollable mental illness.

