#### Drop-Out Criteria

(1) Those who do not comply during the trial have an impact on the evaluation of effectiveness and safety;(2) Those who withdraw themselves during the trial;(3) Those who combine drugs, especially drugs that have a large effect on test drugs, affect effectiveness and safety evaluation;(4) Those who withdraw from the trial, do not receive follow-up, or die before the end of the treatment course for other reasons;(5) Those with incomplete information that affects the evaluation of effectiveness and safety;

The investigators will continue to evaluate the safety after they have been dropped out.

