### Interventions

Patients in the O+YYJD group will receive osimertinib and YYJD granule. Patients in the O+placebo group will receive osimertinib and placebo.

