As a complementary and alternative medicine, TCM is widely used in cancer treatment in China, which has shown the effects of reducing chemotherapy toxicity, enhancing tumor treatment response, improving quality of life, and prolonging survival (Zhang et al., 2018). In the CATLA study, we found that the combination of EGFR-TKIs (gefitinib, erlotinib, or icotinib) and CHM YYJD as first- and second-line therapy significantly prolonged PFS and ORR versus EGFR-TKIs alone. The median PFS was prolonged by 5 months as first-line treatment. At the same time, the side effects of EGFR-TKIs, including fatigue, loss of appetite, diarrhea, pruritus, and skin rash, were reduced (Jiao et al., 2019). Nowadays, the advantage of the third-generation EGFR-TKI, osimertinib, over the first-generation EGFR-TKI is that it overcomes the T790M resistance mutation and has better clinical efficacy in the treatment of advanced NSCLC patients with EGFR mutation-positive. It is reasonable to speculate that YYJD may also have the effect of reducing toxicity and increasing the efficiency of osimertinib.

Qi and Yin deficiency syndrome is one of the most common deficiency syndromes in TCM, manifesting as a pathological state in which both qi and yin deficiency coexist. The typical symptoms are cough, less sputum, fatigue, shortness of breath, dry mouth with less drinking, spontaneous sweating, reddish tongue, or tongue with teeth imprints, thready and weak pulse (Zheng, 2002). Meanwhile, the types of TCM syndromes under EGFR mutations in lung adenocarcinoma are dominated by Qi and Yin deficiency syndrome, and treatment should pay attention to tonifying Qi and nourishing Yin (Wang and Xu, 2017). YYJD is a CHM compound based on TCM theory that mainly exerts the effects of tonifying Qi, nourishing Yin, and detoxifying. In the subgroup analysis of the CATLA study, we found that YYJD had a better clinical benefit for advanced NSCLC patients with EGFR-sensitive mutations, extending median PFS by 16.26 months (Jiao et al., 2019). In addition, most trials have shown that the combination of EGFR-TKIs with oral CHM that tonifies Qi and/or nourishes Yin significantly delays acquired resistance while increasing the ORR of EGFR-TKIs (Lu et al., 2021). Therefore, in the design of this study, the intervention was set as YYJD with greater clinical benefit in order to minimize the impact of TCM syndrome differentiation on outcomes.

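### The listed entry criteria do not expressly exclude current non-study Chinese herbal medicine, and the only stated response to its later use, drop-out, conflicts with the intention-to-treat analysis of PFS

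*Protocol article*

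**What the plan says.** The objective, in the Introduction, is that the study "will determine whether the addition of CHM YYJD to third-generation EGFR-TKI osimertinib (O+YYJD) prolongs PFS compared with osimertinib plus placebo". Under Interventions, "Patients in the O+placebo group will receive osimertinib and placebo", and the Placebo section describes granules with no medicinal content.

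The Inclusion Criteria list seven items. The fourth is the only one on earlier or current treatment: "Patients must have no treatment for locally advanced or metastatic NSCLC". The Exclusion Criteria list five items: other malignancy, symptomatic brain metastases, cardiac disease, active infection and, last, "Those with a history of uncontrollable mental illness". Neither list names herbal medicine or sets an interval free of it.

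The article describes background use twice. The Introduction says "Chinese herbal medicine (CHM) has been used in Chinese NSCLC patients treated with EGFR-TKIs for more than 10 years" and credits it with delaying resistance. The Discussion says "TCM is widely used in cancer treatment in China".

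For non-study drugs during the trial, the Drop-Out Criteria include "Those who combine drugs, especially drugs that have a large effect on test drugs, affect effectiveness and safety evaluation". Of patients who have dropped out, the same section says "The investigators will continue to evaluate the safety after they have been dropped out". The Statistical Analysis section states that primary and secondary outcomes will be analysed by intention-to-treat, full analysis set and per-protocol principles.

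**The concern.** The planned contrast is osimertinib with YYJD against osimertinib without active herbal medicine. For that contrast to hold, the rules must say what happens to herbal medicine taken outside the trial. The setting makes this more than a formality. On the article's own account, herbal medicine is common in these patients and acts on the primary endpoint. Six of the eight sites are traditional or integrated Chinese medicine institutions by name or affiliation.

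Two different harms are possible, depending on how a site handles a user:

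- **The user stays on study and in the analysis.** The PFS contrast may be diluted, and a null result would be harder to read. The quality-of-life, TCM syndrome score and adverse-event comparisons could be blurred in the same way.
- **The user is dropped and PFS assessment ends.** Follow-up stops for a reason that may be linked to how the patient is doing, so the censoring may be informative. The bias could go either way.

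**Working it through.** **1. The plan's own figure.** The Sample Size section gives median PFS of 18 and 23 months, 18 months of recruitment, 30 months in total, α 0.05 (two-sided per Statistical Analysis), power 80%, 1% censoring per month, and N = 314.

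- With exponential PFS, HR = 18/23 = 0.783 and ln HR = −0.245.
- Schoenfeld events = 4 × (1.960 + 0.842)² / 0.245² ≈ 523.
- The mean event probability under the stated accrual and censoring is about 0.459, so N ≈ 523 / 0.459 ≈ 1,140.
- The stated 314 patients give about 144 events and about 31% power.

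The 314 is therefore not reproduced. That shortfall is a separate matter and exists with no outside herbal use at all. It is given here only as the baseline for step 3.

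**2. What the entry rules cover.**

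| Herbal use at screening | Covered by inclusion criterion 4? |
|---|---|
| Taken as treatment for the advanced cancer | Can be read as barred |
| Taken for cough, fatigue or appetite | Not barred by the wording |
| Taken since earlier-stage disease | Not barred by the wording |

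No exclusion criterion fills the last two rows. Use that ends before randomisation should balance between the arms. Only use that continues afterwards can dilute the effect.

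**3. Size of dilution if use continues.** Let f₀ and f₁ be the shares of placebo and YYJD patients using outside herbs, and b₀ and b₁ the effects of those herbs on the log hazard in each arm. Approximately:

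ln HR(observed) = ln HR + f₁b₁ − f₀b₀

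- *Equal use, additive effect* (f₁ = f₀, b₁ = b₀): the last two terms cancel and there is no dilution.
- *Upper bound* (f₁b₁ = 0, b₀ = ln HR): ln HR(observed) = (1 − f₀) × ln HR. The term f₁b₁ is zero either when nobody in the YYJD arm uses outside herbs or when such herbs add nothing to YYJD.
- *Half activity* (f₁b₁ = 0, b₀ = 0.5 × ln HR): ln HR(observed) = (1 − 0.5f₀) × ln HR.

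The placebo median at full activity solves (1 − f₀)·exp(−t ln2/18) + f₀·exp(−t ln2/23) = 0.5. The rate of use is not in the article, so f₀ is shown as an assumed range.

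| f₀ | HR, upper bound | Placebo median (months) | Difference from 23 | HR, half activity |
|---|---|---|---|---|
| 0% | 0.783 | 18.0 | 5.0 | 0.783 |
| 10% | 0.802 | 18.4 | 4.6 | 0.792 |
| 20% | 0.822 | 18.9 | 4.1 | 0.802 |
| 30% | 0.842 | 19.3 | 3.7 | 0.812 |
| 40% | 0.863 | 19.8 | 3.2 | 0.822 |

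In the upper-bound case, required events rise by 1/(1 − f₀)²: 1.23-fold at 10% and 2.04-fold at 30%. Power at N = 314 falls from about 31% to about 26% and 17%.

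**4. The stated response set against the analysis.** The drop-out criterion is generic, acts after randomisation, and turns on a judgement that evaluation is affected. After drop-out, only safety evaluation is said to continue. Intention-to-treat needs every randomised patient followed for PFS whatever else they take. The two sections cannot both be followed as written unless PFS assessment also continues, and the article does not say that it does.

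**The case against.** The strongest reply is that this is a condensed article. Protocol v2.0 is not shown and may hold a list of prohibited and concomitant medication, and the case report form may already have a field for it. That stands as a reason for moderate confidence. It does not remove the point: the article sets out numbered eligibility and drop-out criteria, and as listed they leave the tested class of treatment unaddressed.

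A reader might infer three stronger things that the document does not support:

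- **That the criteria admit current herbal users.** They do not say so. Criterion 4 can be read to bar herbs taken against the advanced cancer, and no section permits non-study herbs. The accurate statement is that other herbal use is not expressly excluded.
- **That the placebo arm is not herbal-free and the effect is diluted.** No rate of use is given. The remark about herbal use with EGFR-TKIs concerns patients already on those drugs, not untreated patients at entry. The trial is blinded with a matching placebo, and centre is an allocation factor, so outside use could well be similar in both arms. Blinding does not fully settle the matter, because equal use still dilutes if outside herbs add less on top of YYJD.
- **That the harm is simply dilution.** If users are dropped, the risk is informative censoring, with no fixed direction.

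It is also fair to say that full activity is generous to arbitrary outside herbs, given that YYJD is a specific 22-component formula. The half-activity column shows how much smaller the effect could be.

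**Conclusion.** The point holds in limited form. The listed criteria do not expressly exclude current non-study herbal medicine taken for symptoms or since earlier disease, although the article describes such medicine as widely used and active with EGFR-TKIs. Dilution of the PFS contrast is possible but not shown. It requires use after randomisation by patients who stay in the analysis, and that use must be either commoner in the placebo arm or less additive to YYJD. The bounding case takes the hazard ratio from 0.78 to about 0.80 to 0.86 for 10% to 40% use; half activity gives about 0.79 to 0.82; equal additive use gives no change. These figures assume exponential PFS, the planned medians, and rates of use that the article does not supply.

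The conflict between the Drop-Out Criteria and the intention-to-treat analysis does not depend on any rate of use and needs correcting in its own right. The correction is worth making, with medium confidence because the full protocol is not shown.

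**What to change.** 1. State in the eligibility criteria whether current non-study Chinese herbal medicine is excluded. If it is, give the interval before randomisation, set by the sponsor.
2. Record any non-study herbal medicine, with product and dates, at baseline and at each existing visit, unless the case report form already does so.
3. Reconcile the Drop-Out Criteria with the Statistical Analysis section. Non-study herbal use becomes a recorded deviation; the patient stays in PFS follow-up and in the intention-to-treat analysis; the record is used only to define the per-protocol set.

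The cost is a protocol amendment, one more case report form item and, if current users are excluded, slightly slower accrual at the traditional Chinese medicine sites. At the status date in the article, 58 of 314 patients had been enrolled, so the change could still cover the remaining 256.

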#### Exclusion Criteria

(1) Those with a history of other malignancies within 5 years;(2) Those with symptomatic brain metastases;(3) Those with congestive heart failure (> class II NYHA heart function), unstable (angina at rest), initial onset (starting within 3 months), angina pectoris, or myocardial infarction occurring within 6 months;(4) Those with active infection (> Grade 2 adverse events according to CTCAE.5.0 version);(5) Those with a history of uncontrollable mental illness.

#### Drop-Out Criteria

(1) Those who do not comply during the trial have an impact on the evaluation of effectiveness and safety;(2) Those who withdraw themselves during the trial;(3) Those who combine drugs, especially drugs that have a large effect on test drugs, affect effectiveness and safety evaluation;(4) Those who withdraw from the trial, do not receive follow-up, or die before the end of the treatment course for other reasons;(5) Those with incomplete information that affects the evaluation of effectiveness and safety;

The investigators will continue to evaluate the safety after they have been dropped out.

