#### Voluntary Withdrawal of Participants

Participants are allowed to withdraw from the trial at any time, according to the informed consent form. Participants who do not formally withdraw from the trial but stop receiving intervention treatment or testing on their own, or are lost to follow-up, are considered to have withdrawn. The reasons for all participants who withdraw from the trial should be identified and documented to the extent possible.

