#### Primary Outcome

PFS: measured with the date of the videography from a random assignment to the date of objective progression or death by the researcher.

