### Statistical Analysis

Data analysis will follow the trial’s statistical analysis plan. All data will be processed by statistical analysis with SAS 9.4 software analysis. Two-tailed *p* values <0.05 are considered statistically significant. The analysis will follow intention-to-treat, full analysis set, and per-protocol subject principles for the evaluation of primary and secondary outcomes. The safety data set that includes all subjects who received at least one treatment after randomization will be used to evaluate safety and tolerance. Missing data will be processed with the multiple imputation method.

The baseline characteristics will be reported according to treatment groups. PFS and OS will be illustrated by the Kaplan–Meier survival curve and compared between groups using the log-rank test. The secondary outcomes will be summarized with frequency, mean, standard deviation, median, and range. At each time point, comparisons between the experimental group and the placebo group will be conducted using the Group t-test or Wilcoxon rank-sum test (for measurement data) and the rank-sum test and CMH test (for count data). Fisher’s exact test will be used to compare tumor response rates between the arms. For PFS, an adjusted Cox regression model will be used to estimate the adjusted HRs for differences between the treatment arms with the selected prognostic factors, including the center, EGFR mutation type, age, sex, EGFR-TKI drugs, smoking status, and ECOG PS.

Safety will be documented in adverse event forms and presented with descriptive statistics for each group. The frequency difference of adverse events between groups will be assessed by the chi-square test or Fisher’s exact test. For different AE severities, a rank-sum test will be performed to analyze the independent ordered multiple category data between the two groups.

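### The drop-out and withdrawal rules conflict with the PFS and OS definitions, the imaging schedule and the intention-to-treat analysis, and risk losing events and efficacy follow-up

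*Protocol article*

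**What the plan says.** All references are to the protocol article.

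- **Drop-Out Criteria** has five items. Item 1 is "Those who do not comply during the trial have an impact on the evaluation of effectiveness and safety". Item 3 is "Those who combine drugs, especially drugs that have a large effect on test drugs, affect effectiveness and safety evaluation". Item 4 is "Those who withdraw from the trial, do not receive follow-up, or die before the end of the treatment course for other reasons". Items 2 and 5 cover patients who withdraw themselves and incomplete information that affects the evaluation. The section ends: "The investigators will continue to evaluate the safety after they have been dropped out". It does not mention imaging, progression or survival after drop-out.
- **Voluntary Withdrawal of Participants** says of patients who have not formally withdrawn that those who "stop receiving intervention treatment or testing on their own, or are lost to follow-up, are considered to have withdrawn".
- **Study Design** and **Outcomes** schedule assessment at baseline, at 4 weeks and every 8 weeks after that, until progression or death. Neither makes an exception for drop-outs.
- **Primary Outcome** runs PFS "from a random assignment to the date of objective progression or death by the researcher", with no restriction on the cause of death.
- **Secondary Outcomes** counts death from any cause for OS, and censors patients lost to follow-up at their last follow-up.
- **Statistical Analysis** says: "The analysis will follow intention-to-treat, full analysis set, and per-protocol subject principles for the evaluation of primary and secondary outcomes".

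**The concern.** Two different things are merged. One is whether a patient still takes the study treatment. The other is whether the patient's outcome is still observed. An intention-to-treat comparison of PFS needs the outcome of every randomised patient whether or not treatment continues. A rule that moves a patient who stops treatment, or takes other drugs, into a withdrawn category with only safety evaluation promised can end the observation that the analysis needs.

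The reasons for such drop-out are unlikely to be unrelated to prognosis. The Discussion says that osimertinib toxicity can lead patients to stop treatment, and that the herbal decoction reduced side effects of the earlier drugs. Stopping could therefore differ between arms even under good blinding.

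Death is the sharpest case. It is a primary-endpoint event in one section and a reason for drop-out in another. Two centres could file the same death differently.

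The planned effect is moderate (18 against 23 months, hazard ratio 18/23 = 0.78), so even a small distortion matters. Scans that were never taken cannot be recovered at analysis.

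**Working it through.** **1. The passages side by side**

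| Situation | Drop-out and withdrawal sections | Rest of the article |
|---|---|---|
| Death before the end of the treatment course for other reasons | Drop-out | PFS event; OS event whatever the cause |
| Stops study treatment on own initiative | Considered withdrawn | Imaging until progression or death; ITT |
| Non-compliance or combined drugs that affect the evaluation | Drop-out; safety evaluation continues | Imaging until progression or death; ITT |

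The first row is a direct conflict. Treatment has no fixed length: the Abstract ends it at progression or death, and the Osimertinib section at progression or intolerable adverse effects. For a patient still on treatment, a death before the end of the course is a death without earlier progression. That is the death component of PFS. The words about other reasons are not defined, so the text does not show which deaths are meant.

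In the second and third rows the conflict lies in what is promised. One part of the article schedules efficacy assessment to progression or death. The other relabels the patient and mentions safety alone.

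**2. Scale**

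The plan gives no expected number of drop-outs. Its only related figure is the 1% average monthly censoring rate under Sample Size. The other inputs from that section are medians of 18 and 23 months, recruitment A = 18 months, total duration T = 30 months and 157 patients per arm. The stated 314 is taken as the planned number. These inputs do not reproduce it (a two-sided Schoenfeld calculation needs 523 events and about 1,139 patients), but that is a separate matter on which this point does not rest.

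Assume exponential PFS, uniform accrual and exponential censoring at η = 0.01 per month. Let λ = ln 2 / median and r = λ + η.

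- Still at risk at the cut-off: S = (e^(−r(T−A)) − e^(−rT)) / (rA)
- PFS event: (λ/r)(1 − S)
- Censored before the cut-off: (η/r)(1 − S)

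| Arm | λ | r | S | Event | Censored |
|---|---|---|---|---|---|
| Control | 0.0385 | 0.0485 | 0.373 | 0.498 | 0.129 |
| Intervention | 0.0301 | 0.0401 | 0.440 | 0.421 | 0.140 |

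Expected events: 157 × (0.498 + 0.421) ≈ 144.
Censored under the allowance: 157 × (0.129 + 0.140) ≈ 42.

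**3. When would it bias the hazard ratio?**

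This is an illustration; the shares are assumptions, not figures from the article. The true hazard ratio is 1, both medians are 18 months, and an assumed share of patients in each arm is censored one month before their event.

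| Share, placebo | Share, YYJD | Hazard ratio from Cox model |
|---|---|---|
| 5% | 5% | about 1.00 |
| 10% | 10% | about 1.00 |
| 5% | 10% | about 0.95 |
| 5% | 15% | about 0.90 |
| 15% | 5% | about 1.11 |

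Equal shares cost events but leave the ratio near 1. Unequal shares move it in either direction.

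**The case against.** The strongest reply is that nothing in the article says drop-outs are censored for PFS, removed from the intention-to-treat set or no longer imaged. The article names intention-to-treat first, counts death without regard to cause, and schedules imaging to progression or death without exception. Drop-out may be only a disposition label, or may matter only for the per-protocol set. Items 1, 3 and 5 apply only where the evaluation is affected, and the withdrawal section covers patients who stop on their own, not every discontinuation.

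All of this stands. A reader might infer that the primary PFS analysis is informatively censored and is not intention-to-treat. The documents do not support that. They state no censoring rule for PFS, and the only one given is for OS.

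A reader might also infer a bias in favour of the decoction. That is not supported either. Such a result needs more of its patients than placebo patients to leave just before progression, and the article gives no such shares. Its own remark on reduced side effects could point the other way. Nor are the 42 patients an estimate of those caught by these rules, or evidence that their censoring is informative.

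Finally, which analysis set decides the primary test may properly be left to the statistical analysis plan, so it is not part of this point.

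The reply does not remove the contradiction. Naming intention-to-treat does not supply outcomes that were not collected, and centres will act on the drop-out rules as they read them.

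**Conclusion.** The point holds as a conflict within the protocol article that carries a risk for the primary endpoint. It is not a demonstrated bias. The drop-out and withdrawal sections cannot be applied as written together with the imaging schedule, the PFS and OS definitions and the intention-to-treat principle. If centres follow them literally, PFS events and efficacy follow-up could be lost for reasons tied to prognosis.

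The size and direction of any effect on the hazard ratio cannot be derived from the documents, and it would be near zero if the losses were equal between arms. The comparison of about 42 censored patients with about 144 events rests on the plan's own medians, durations and 1% rate, with exponential times and uniform accrual assumed. It shows scale only.

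The conflict is worth settling early: 58 of 314 patients had been enrolled by 23 December 2021, so most follow-up still lay ahead at that date.

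**What to change.** Reconcile the sections by amendment:

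1. Record stopping study treatment and withdrawing consent to follow-up as two separate things, each with date and reason. Stopping treatment, non-compliance or use of other drugs should not by itself end efficacy follow-up.
2. Take death off the drop-out list, and state that every death counts as an OS event and, where no progression came first, as a PFS event.
3. State that the imaging already scheduled continues to progression, and survival follow-up continues after that, for all randomised patients who have not refused follow-up. Extend the closing sentence of the Drop-Out Criteria from safety to efficacy, so that the intention-to-treat analysis can be carried out.

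The cost is amendment wording, notice to the eight centres, and some further scans and contacts in patients who stop study treatment. No dose or treatment rule changes. The downside is a modest follow-up burden for those patients.
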